#### Exclusion criteria

Patients will be excluded from the study if they have severe cardiac disease (New York Heart Association class III or greater), angina, pre-existing osteoporosis with T-score at or below -2.5, stable bone lesion, uncontrolled hypertension (blood pressure > 160/95 mm Hg), moderate to severe aortic stenosis, acute illness or fever, uncontrolled atrial or ventricular dysrhythmias, uncontrolled sinus tachycardia (> 120 beats per minute), third-degree atrio-ventricular heart block, active pericarditis or myocarditis, recent pulmonary embolism, deep vein thrombosis, uncontrolled diabetes, uncontrolled pain, cognitive impairment, history of falls due to balance impairment or loss of consciousness, severe neuromusculoskeletal conditions that limit their ability to perform walking exercise (including ataxia, peripheral or sensory neuropathy, unstable bone lesion, severe arthritis, pathological lower limb fractures within 6 months, lower limb amputation).

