#### Randomization of group assignment

GRA1 will be blinded to the group assignments of the participants. Therefore, after the baseline assessment and pedometer instruction, GRA2 will be responsible for the randomized group assignment. GRA2 will assign the participant the first available number from a randomly generated list consisting of "1" and "2". Number "1" is designated as the Exercise Group that will receive instructions in setting up an individualized 12-month home-based walking exercise program in addition to their daily activities. Number "2" is designated as the Control Group that will be advised to perform daily activities as usual and follow the standard medical advice from their attending physician.

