#### Exercise group protocol

GRA2 will assess the baseline health and fitness of the participants of the exercise group by using an exercise screening form that includes the revised Physical Activity Readiness Questionnaire (PAR-Q), [23] and other screen questions for exercise contraindications and precautions. If any exercise contraindication is identified (e.g. shortness of breath, severe headache, sudden onset of numbness or weakness), the participant will be excluded from the study and referred to their family physician for investigation. If any exercise precautions is identified (e.g. fever, severe cachexia, extreme fatigue, sickness or bone pain), high-intensity or high-impact exercise will be initially avoided. If severe nausea or calf pain is present, the participants will be advised to consult their family physician for further investigation and clearance prior to beginning the exercise program.

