The Exercise Group will follow a walking exercise program that comprises a progressive structured exercise protocol and progressive target daily step counts. The structured exercise protocol will initially begin with a 10-minute walking session, 3 sessions per week. The Exercise Group participants will be instructed to perform a 5-minute warm-up period by walking slowly prior to the 10-minute walking session. There will also be a 5-minute cool-down period by walking slowly, followed by a stretching routine after the 10-minute walking session. The stretching instruction sheet will be provided to the participants. GRA2 will also educate and demonstrate to the participants how the stretches are to be done. During the warm-up/cool-down periods, the participants will maintain an exertion level between 7.5 and 8 on the Borg Scale of Ratings of Perceived Exertion (RPE) [24] (i.e., extremely light level of exertion). During the 10-minute walking session, the participants will gradually increase the walking speeds until they attain and maintain an RPE level between 9 and 13 (i.e., very light to light exertion) according to their baseline physical activity level (sedentary, moderately active, or active) as reported on their self-reported physical activity questionnaire. Sedentary individuals will walk at RPE level 9 (very light exertion), moderately active individuals will walk at RPE level 11 (light exertion), and active individuals will exercise at RPE level 13 (somewhat hard exertion). Each participant's exercise level will be progressed every two week, first in frequency (1-day increment), then duration (5-minute increment), and lastly RPE level. Based on the set progression protocol, the Exercise Group participants will be performing five walking exercise sessions per week, 30 minutes walking per session, and will attain RPE level 15 (heavy exertion) during the walking session by around 18 to 20 weeks. This level of exercise protocol will be maintained for the rest of the study period. The participants are instructed to record the date, start time, exercise duration and maximum RPE attained during each session in an exercise daily log. The participants will also be encouraged to walk at their chosen pace at times outside their structured exercise protocol so as to achieve their assigned target daily step counts. The initial target will be set at 5,000 steps for sedentary individuals, 6000 steps for moderately active individuals, and 7,000 steps for active individuals. The target daily step counts will be progressed every two weeks (1000-steps increment) up to a maximum daily target of 10,000 steps. The participants will be counseled on the warning symptoms of impending cardiovascular events including chest pain or discomfort, shortness of breath, dizziness, severe headache, sudden onset of numbness or weakness, or calf pain suggestive of deep vein thrombosis. They will be strongly advised to discontinue the exercise program and report these symptoms to their attending physician and GRA2 immediately. An exercise advice and instructions sheet will be provided to the Exercise Group participants.

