#### Follow-up sessions

GRA1 will schedule follow-up sessions for all participants at 3, 6, 9, and 12 months after ADT initiation. Primary outcome (HRQOL and physical function) and secondary outcome variables (physical fitness, psychosocial-cognitive functions, and physical activity) will be re-assessed during the follow-up sessions.

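### As the exercise screen is written, a man with fever may start the walking programme; deferring the start until recovery is a small, cheap safety gain

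*Protocol article*

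**What the plan says.** Under *Exclusion criteria*, the list of conditions that bar entry includes "moderate to severe aortic stenosis, acute illness or fever". Under *Recruitment*, a clinical research nurse checks eligibility before the man is passed on for a baseline visit. Allocation comes later: "after the baseline assessment and pedometer instruction, GRA2 will be responsible for the randomized group assignment".

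Under *Exercise group protocol*, men allocated to exercise are then screened again. Three groups of findings lead to three actions:

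- Contraindications lead to exclusion from the study and referral to the family physician.
- Precautions limit intensity only: where any "precautions is identified (e.g. fever, severe cachexia, extreme fatigue, sickness or bone pain), high-intensity or high-impact exercise will be initially avoided".
- Two further symptoms hold the start: "If severe nausea or calf pain is present, the participants will be advised to consult their family physician for further investigation and clearance", to be obtained before the programme begins.

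The same section sets the opening dose: "The structured exercise protocol will initially begin with a 10-minute walking session, 3 sessions per week". Men are to raise their speed until they "attain and maintain an RPE level between 9 and 13 (i.e., very light to light exertion"), with the level set by baseline activity. Men are also told which symptoms mean they must stop and report; these are "warning symptoms of impending cardiovascular events including chest pain or discomfort, shortness of breath, dizziness, severe headache", sudden numbness or weakness, and calf pain. Under *Follow-up sessions*, "GRA1 will schedule follow-up sessions for all participants at 3, 6, 9, and 12 months after ADT initiation".

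**The concern.** Fever is serious enough to keep a man out of the trial, yet by the stated rule it does not delay his first exercise session once he has been allocated. The protocol already has a rule that holds the start, and it applies that rule to severe nausea and calf pain but not to fever. The action it does attach to fever limits something that is hardly part of the first weeks.

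What is at stake is participant safety on a small scale: a man who is temporarily ill could begin structured walking, with a daily step target on top, when waiting a few days would cost almost nothing. The screen is run by a graduate research assistant, so the written rule carries some weight. No estimand, error rate, sample size or analysis is involved.

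**Working it through.** The protocol gives no figure on this point, so there is none to reproduce. The check is a comparison of the stated rules, followed by a rough sizing.

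**Step 1: order of events.** Eligibility is confirmed by the nurse (*Recruitment*). The baseline session is scheduled after that (*Baseline assessment session*). Randomisation follows the baseline session (*Randomization of group assignment*). The exercise screen is given only to men in the Exercise Group (*Exercise group protocol*). A fever can arise between the eligibility check and the screen, so the exclusion criterion makes the case rarer but does not remove it.

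**Step 2: what each rule does with fever.**

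| Step | Finding | Stated action |
|---|---|---|
| Eligibility | Acute illness or fever | Not enrolled |
| Exercise screen | Fever or sickness | Limit on intensity and impact at first |
| Exercise screen | Severe nausea or calf pain | Start held until cleared |
| During the programme | Cardiovascular warning symptoms | Stop and report; fever not listed |

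**Step 3: what the limit removes.** Sedentary men start at RPE 9, moderately active men at 11 and active men at 13. RPE 15 is reached only at around 18 to 20 weeks. A limit on intensity at first therefore takes little or nothing from the opening sessions. The rule does not tie its end to recovery.

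**Step 4: size for one man.** Assume a fever of d = 2 to 7 days and a start straight after the screen; the documents give neither.

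- Sessions within the fever = 3 × d/7. For d = 2: 6/7 = 0.9. For d = 7: 21/7 = 3.0. So about 1 to 3 sessions.
- Main walking = 1 to 3 sessions × 10 min = 10 to 30 min.
- With 5 min of warm-up and 5 min of cool-down, each session has 20 min of walking, so 20 to 60 min in all. The initial daily targets of 5,000 to 7,000 steps come on top.

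**Step 5: number of men.** Sixty men are planned; an equal split, which is assumed, gives 60/2 = 30 in the Exercise Group. Assume 1% to 5% have a fever at the screen (no rate is given): 30 × 0.01 = 0.3 and 30 × 0.05 = 1.5 men.

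**Step 6: what deferral would cost in exercise.** Each affected man loses 2 to 7 days. Of the first 3 months that is 2/91 = 2.2% to 7/91 = 7.7%; of 12 months, 2/365 = 0.5% to 7/365 = 1.9%.

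**The case against.** The strongest reply is that the section sets a limit on intensity and does not mention timing. It never says that a man with fever should begin. Day-to-day handling of temporary illness would normally sit on the exercise screening form or the advice sheet, and a condensed article need not reproduce either. This stands in part: those papers may already tell men to wait, so the point covers only the rule as stated. It does not dispose of the point, because the article is not silent on fever. It puts fever in a named group, gives that group's action, and puts other symptoms in a group whose action does hold the start.

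A second reply is that existing safeguards narrow the gap. Eligibility has been checked, the programme is paced by perceived exertion so a man who feels ill can slow down, and safety calls are made every two weeks for the first 20 weeks. All true, and a reason to rate the point low. But a fever of 2 to 7 days can be over before the first call. A man who is febrile at the baseline visit may also have done the six-minute walk test there already, and deferring the programme leaves that untouched.

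A third reply is that the documents show no harm from ten minutes of light walking with a fever, and that treating fever differently from severe nausea is a clinical judgement. That also stands as far as it goes. The exclusion criterion gives no reason, so it cannot be read as evidence of a specific hazard.

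Finally, *sickness* may mean mild nausea or feeling unwell rather than acute illness, since severe nausea is dealt with in the next sentence. This bears on the remedy: the precaution list should stay as it is.

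**Conclusion.** The point holds as a minor safety inconsistency. By the stated rule a man with fever at the exercise screen may start, while fever bars entry earlier and severe nausea or calf pain holds the start at the same screen. Under the assumptions above it concerns 0.3 to 1.5 men and about 1 to 3 short sessions each. The fever rate, fever length, equal split and immediate start are all assumed, and the section gives no start date.

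A reader might infer that the protocol contradicts itself. It does not: the exclusion criterion applies at recruitment and the precaution applies after randomisation, so both can be followed. A reader might also infer that the protocol directs men with fever to exercise, or that the trial's results are at risk. The text does neither: it permits a start by leaving the timing open, and nothing in the statistical analysis depends on it. The change is worth considering because it is cheap, not because the risk is large.

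**What to change.** Keep the precaution list under *Exercise group protocol* as it is, including fever and sickness, and add after it:

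> *If fever or acute illness is present, the start of the exercise program will be deferred until it has resolved, and the initial limit on intensity and impact will still apply from then; the participant remains in the Exercise Group and in follow-up.*

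Keeping fever in the list matters: if it were deleted, a man who has just recovered would lose the initial limit that the current text gives him. Keeping the man in his group means that the change adds no exclusion after randomisation.

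The cost is one sentence in the protocol and the matching line on the screening form. For each man affected there is a delay of a few days and one extra call to confirm recovery. Visit dates do not move, because they are counted from ADT initiation, so a deferred man has a few days less exercise before each visit. If the screening form or advice sheet already says to wait, the protocol should simply be made to match it.

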### Participants

#### Inclusion criteria

Patients will be included in the study if they are men aged 50 years or older, diagnosed with adenocarcinoma prostate cancer, and who will initiate and receive continuous ADT (LHRH agonist alone or in combination with another anti-androgen) for at least 12 months after recruitment. Patients will be required to provide written informed consent to participate in the study.

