#### Recruitment

A total of 60 patients will be consecutively recruited during the initial 3-months of the study from office visits at Cancer Care Manitoba. The attending physician will screen the patients for inclusion criteria (men aged 50 or older), diagnosed with prostate adenocarcinoma, will initiate and receive continuous ADT (LHRH alone or in combination with another anti-androgen for at least 12 months). If the patients meet the preliminary inclusion criteria, the physician will refer them to a clinical research nurse who will confirm that all inclusion and exclusion criteria are met, explain the study protocol, provide information sheet, and obtain written informed consent from any patients who would like to participate in the study. The clinical research nurse will provide a graduate research assistant (GRA1) with the signed consent forms and contact information of the patients who have agreed to participate in the study.

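### Baseline activity category sets each man's walking targets, under one step and session ceiling for all, but is used neither in the allocation nor in the primary analysis

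*Protocol article*

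**What the plan says.** All references are to the protocol article.

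- **Eligibility.** Inclusion criteria: "Patients will be included in the study if they are men aged 50 years or older, diagnosed with adenocarcinoma prostate cancer", starting continuous ADT. The Exclusion criteria cover cardiac and other safety conditions, osteoporosis, and "severe neuromusculoskeletal conditions that limit their ability to perform walking exercise". Neither these sections nor Recruitment sets an upper limit on activity.
- **Tiers.** Exercise group protocol sorts men as sedentary, moderately active or active from a self-report questionnaire. Starting RPE is 9, 11 or 13. For steps: "The initial target will be set at 5,000 steps for sedentary individuals, 6000 steps for moderately active individuals, and 7,000 steps for active individuals".
- **Common end point.** Targets rise by 1,000 steps every two weeks, "up to a maximum daily target of 10,000 steps". All men progress to "performing five walking exercise sessions per week, 30 minutes walking per session", at RPE 15, and stay there to the end of the study.
- **Allocation.** Randomization of group assignment describes one randomly generated list of 1s and 2s, used after the baseline assessment. The walking programme comes on top of usual activities. Controls are told to carry on as usual.
- **Analysis.** Statistical analysis gives a mixed MANOVA (Group X Time) for the primary outcomes and names no term for baseline activity.
- **Size.** "A total of 60 patients will be consecutively recruited during the initial 3-months of the study".

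**The concern.** The efficacy question rests on a difference in walking between the arms. Targets follow a broad self-reported tier rather than the man's own measured level, and the step and session ceiling is the same for all. A man already walking close to that ceiling is eligible. In the Exercise Group the step component changes little for him. In the Control Group he may simply go on walking. Such men may contribute less contrast than the others.

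The category is also a natural prognostic factor. It decides the starting targets and plausibly relates to 6MWT, SPPB and fatigue, and to how these change during ADT. It is obtainable for every man before allocation, but the described design makes no use of it for balance or precision. With 60 men, chance imbalance between arms is not negligible.

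**Working it through.** The document gives no power calculation, so there is no stated figure to reproduce.

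**1. How soon the ceiling is reached (document figures only).**

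| Tier | Start | Increments to 10,000 | Weeks (2 per increment) |
|---|---|---|---|
| Sedentary | 5,000 | 5 | 10 |
| Moderately active | 6,000 | 4 | 8 |
| Active | 7,000 | 3 | 6 |

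Sessions go from 3 to 5 a week (2 increments) and from 10 to 30 minutes (4 increments of 5 minutes): 6 x 2 = 12 weeks in every tier. A man who already takes 10,000 steps starts on a target 10,000 - 7,000 = 3,000 below his habit, and the step target never exceeds that habit. Intensity is different: even the active tier has room from RPE 13 to 15.

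**2. Possible dilution (illustration).** Let f be the share of men near the ceiling and r the fraction of the effect they still gain. Neither is in the document. The average effect is multiplied by (1 - f) + f*r, and the information by the square of that. Power assumes 30 per arm, two-sided alpha 0.05 and a standardised effect of (1.960 + 0.842) x sqrt(2/30) = 0.72, which gives 80% without dilution.

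| f | r | Effect multiplier | Information | Power |
|---|---|---|---|---|
| 0 | - | 1.00 | 1.00 | 80% |
| 0.2 | 0 | 0.80 | 0.64 | 61% |
| 0.2 | 0.5 | 0.90 | 0.81 | 71% |
| 0.4 | 0 | 0.60 | 0.36 | 39% |
| 0.4 | 0.5 | 0.80 | 0.64 | 61% |

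The direction follows whenever r is below 1. The size depends entirely on f and r.

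**3. Chance imbalance in the category.** Suppose a share p of the 60 men is active and the arms are 30 and 30. The number of active men in one arm has variance 30 x p x (1 - p) x 30/59.

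- p = 0.2: 4.8 x 0.508 = 2.44, SD 1.56. The difference in counts between arms has SD 3.1, which is 3.1/30 = 10 percentage points.
- p = 0.4: 7.2 x 0.508 = 3.66, SD 1.91. The difference has SD 3.8, or 13 percentage points.

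A difference in baseline level alone falls in the Group main effect, not in Group X Time. The interaction is affected only if men in different categories change differently over the year. The typical chance shift is then 0.10 to 0.13 times that difference in change. For the same reason, a covariate fixed at baseline helps the interaction test only if its own interaction with time is in the model.

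**The case against.** The strongest reply is that the programme does not stop at volume. Its end point includes RPE 15, so a man who walks the same distance more gently has not reached it, and the sessions are described as additional to usual activity. Phone surveys also guide adjustment of both the exercise and the step protocols. Active controls may slow down during ADT, which the Background links to fatigue and functional decline, so maintained activity in the Exercise Group would itself be a contrast. All of this stands, and zero gain in active men cannot be assumed. Still, the stated step maximum applies to all, and nothing described prevents a man's usual walks from being logged as sessions.

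A reader might infer that a null result could not be told apart from having enrolled men who already exercised. The document does not support this. All participants keep pedometer logs, RAPA is taken at every assessment, and both are analysed by Group X Time. These data would help show whether activity separated, though they would not restore lost power.

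A reader might also infer that already-active men must be excluded. The document does not support that either. Their inclusion is deliberate, and the trial is called a pilot in Methods/Design. At shares of 20% to 40%, an exclusion would require 60/0.8 = 75 to 60/0.6 = 100 otherwise eligible men, with recruitment planned over three months, and it would narrow the population.

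Finally, covariates and stratification detail are often left to a fuller document. If one already uses the activity category, the main recommendation is met.

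**Conclusion.** The point holds as a modest design improvement, not as an error that invalidates the trial. It is firm that no upper activity limit exists, that active men share the common step and session ceiling, and that the described allocation and primary analysis do not use the category. It is also firm that the step target asks nothing more of a man already at 10,000 steps.

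Dilution is possible and its direction is clear, but its size cannot be derived. The 20% to 40% shares, the zero or half gain, and the power inputs are all assumptions. The expected gain from using the category is better balance and some precision, its amount depending on how strongly category predicts change. It would not remove dilution. This rests on the tiering questionnaire being completed at baseline by men in both arms. RAPA, the only activity questionnaire named, is collected then, but Exercise group protocol does not name the instrument.

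**What to change.** 1. Assign every man, in both arms, to sedentary, moderately active or active from the baseline questionnaire before allocation, and name the instrument and the rule.
2. Either stratify the random list by this category, with permuted blocks within each category (separate unblocked lists would not secure balance), or include the category and its interaction with time as a baseline covariate in the primary Group X Time comparisons. If stratified, carry the category into the analysis as well. State in advance how a sparse category will be merged; 60 men over three categories is 20 each on average.
3. Report the group difference in step counts and in RAPA over time by baseline category, as a descriptive check on dilution and not as a test.

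The cost is small: no new measurement, a few degrees of freedom, and a slightly more complex list. Whether to restrict entry by baseline activity remains a choice for the trial team. If they do, the criterion should take account of the intensity component as well as volume.
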